VACPAC study

A Multi-Institutional Study on the Safety and Effectiveness of Prophylactic Negative Pressure Wound Therapy for Perineal Wounds

prophylactic Vacuum-Assisted Closure on Perineal wound after Abdominoperineal resection for rectal Cancer

Research Protocol

Principal Investigator: Department of Surgery, Graduate School of Medicine, Kyoto University

Professor, [name]

Version 1.0 January 20, 2025

Revision history

| Version number | Date of creation (revision) |
| --- | --- |
| Version 1.0 | January 20, 2025 |

Ethical Principles

All personnel involved in this study shall comply with the "Clinical Trials Act (Act No. 16 of 2017)" (promulgated on April 14, 2017) and the "Enforcement Regulations on the Clinical Trials Act (Order of the Ministry of Health, Labour and Welfare No. 17 of 2018)" (promulgated on February 28, 2018), as well as other relevant legal regulations. Additionally, they shall adhere to applicable ethical guidelines, including the "World Medical Association Declaration of Helsinki" (revised in October 2013).

Overview

| Objective | | To prospectively evaluate the safety and effectiveness of prophylactic negative pressure wound therapy (pNPWT) for perineal closure wounds following abdominoperineal resection for rectal malignancies. |
| --- | --- | --- |
| Study Phase | | Phase 2 |
| Planned Start Date for Patient Enrollment | | December 1, 2024 |
| Study Duration | | From the date of public disclosure of the study plan to May 31, 2026 |
| Planned Number of Participants | | 50 cases |
| Study Type | | Interventional study |
| Study Design | | Single arm study  Open (masking not used)  Uncontrolled  Single assignment  Prevention purpose |
| Coverage of Costs | | No additional medical expense burden on participants |
| Countries of Recruitment | | Only Japan |
| Key  Inclusion & Exclusion Criteria | Inclusion Criteria | 1) Patients undergoing abdominoperineal resection (APR) for rectal malignancies.  2) Patients meeting the insurance coverage criteria for the PREVENA incision management system, specifically:  (a) Patients who underwent neoadjuvant therapy (chemotherapy, chemoradiotherapy, or both).  (b) Obese patients with a BMI ≥ 30.  (c) Diabetic patients with HbA1c (NGSP) ≥ 7.0%.  (d) Patients receiving steroid therapy.  (e) Patients undergoing chronic maintenance dialysis.  (f) Patients with malnutrition (meeting one of the following criteria):  3) Patients aged 18 years or older, regardless of gender, with an ECOG Performance Status (PS) of 0 or 1.  4) Obtain written consent to participate in the study |
|  | Exclusion Criteria | 1) Emergency surgery cases.  2) Cases with obviously contaminated/infected wounds where primary closure is not advisable.  3) Myocutaneous flap reconstruction is scheduled to be performed.  4) Patients with allergies or hypersensitivity to silver or acrylic adhesives.  5) Other cases deemed inappropriate for study participation by the principal or sub-investigators |
|  | Minimum Age | 18 years |
|  | Maximum Age | None |
|  | Gender | Both male and female participants are eligible |
| Discontinuation Criteria | | 1) The participant was registered but did not receive prophylactic negative pressure wound therapy (pNPWT).  2) The participant requests discontinuation of treatment or withdrawal of consent.  3) The participant is found to be ineligible after the start of treatment.  4) The principal or sub-investigator determines that continuation of the study is difficult for safety or other reasons. |
| Target Disease | | Rectal malignancies |
| Intervention Details | | Following primary suture closure of the perineal wound after APR, prophylactic negative pressure wound therapy (pNPWT) using the Prevena Plus Customizable Kit will be applied for one week. |
| Primary Outcome(s) | | Incidence rate of surgical site infection (SSI) in the perineal wound within 30 days postoperatively. |
| Secondary Outcome(s) | | Incidence of postoperative complications other than perineal SSI.  Postoperative hospital stay duration.  Completion rate of pNPWT. |

Shema

[figure not shown]

Table of Contents

[1. Background and Significance 9](#_Toc191825328)

[1.1. Target Disease and Previous Studies Related to This Research 9](#_Toc191825329)

# Background and Significance

## Target Disease and Previous Studies Related to This Research

The incidence of surgical site infection (SSI) following abdominoperineal resection (APR) for rectal malignancies is high ^(1)(2)^. Among them, perineal wound SSI accounts for 30–64% ^(3)(4)^. Once an SSI occurs, it may lead to an extended hospital stay, increased medical costs, and a decline in the patient’s quality of life ^(5)^. Furthermore, rectal cancer patients requiring APR often have advanced-stage disease and are candidates for adjuvant chemotherapy postoperatively. A delay in initiating chemotherapy due to perineal wound SSI may negatively impact long-term prognosis ^(5)^. Therefore, preventing perineal wound SSI is a critical issue.

Several factors contribute to SSI after APR. Perineal wounds experience significant tension during ambulation, which may lead to wound dehiscence ^(5)^. Additionally, blood and exudates accumulating in the pelvic dead space after organ resection may serve as a source of infection, leading to pelvic abscesses and wound infections ^(4)^. Patients undergoing neoadjuvant therapy, such as neoadjuvant chemotherapy (NAC), neoadjuvant chemoradiotherapy (NACRT), or total neoadjuvant therapy (TNT), may experience delayed wound healing due to tissue damage and immunosuppression ^(6)^.

Various preventive measures for perineal wound SSI have been reported, including omentoplasty and pelvic floor reconstruction using myocutaneous flaps such as the rectus abdominis or gracilis muscle ^(7)(8)(9)^. However, perineal wound SSI remains common even with these approaches. Additionally, myocutaneous flaps require plastic surgical techniques and carry risks such as flap necrosis ^(10)^ and prolonged operative time ^(4)^. Omentoplasty may not be feasible in cases involving inflammation or prior omentectomy ^(11)^. Given these limitations, a novel approach to reduce perineal wound SSI is necessary.

## Positioning and Significance of This Study and the Investigational Device

Negative pressure wound therapy (NPWT), also known as vacuum-assisted closure (VAC), is a non-invasive method that promotes wound healing by applying negative pressure in a closed environment ^(12)^. NPWT has shown favorable outcomes in treating chronic and complex wounds, such as diabetic foot gangrene and mediastinitis after cardiac surgery ^(13)^. In gastrointestinal surgery, NPWT has been effective in managing open midline wounds following peritonitis and perineal open wounds after APR ^(14)^.

Recently, prophylactic NPWT (pNPWT) has gained attention for use in patients at high risk of wound complications. The 2018 Perioperative Management Guidelines for SSI Prevention in Gastrointestinal Surgery by the Japan Society for Surgical Infection suggest that pNPWT may reduce incisional SSI in gastrointestinal surgery ^(15)^. The proposed mechanisms of pNPWT include reducing wound tension by approximating wound edges, decreasing hematoma and seroma formation in the subcutaneous space, and creating a sealed environment that protects against external contamination. These combined effects are believed to lower the risk of SSI ^(16)(17)^. Observational studies and randomized controlled trials (RCTs) have been conducted in gastrointestinal surgery for non-infected closed wounds ^(18)(19)^. However, there are few reports specifically on pNPWT for perineal wounds after APR. Some studies suggest that pNPWT may reduce perineal wound SSI rates by 25–30% ^(20)^, but these studies have small sample sizes and lack definitive evidence.

## Development of This Study Plan

In March 2021, the Prevena Incision Management System (IMS) (3M, St. Paul, Minnesota) became the first pNPWT device approved in Japan. Prior to this clinical trial, a preliminary study was conducted at Fukuoka University Hospital, where Prevena was applied to perineal closed wounds after APR. In a control group of 117 patients who underwent primary closure alone without pNPWT, perineal wound SSI was observed in 24%. In contrast, in the pNPWT group (10 patients), no cases of perineal wound SSI were reported.

This study aims to prospectively evaluate the safety and effectiveness of pNPWT for perineal closed wounds after APR, thereby clarifying its effectiveness, indications, and clinical significance. Since April 2022, pNPWT has been covered by the Japanese insurance system, and its use for SSI prevention in high-risk patients may become the standard of care. The data obtained in this study will provide the basis for a future large-scale trial in gastrointestinal surgery, further establishing the efficacy and safety of pNPWT for perineal and other surgical wounds.

# Objective

This study aims to prospectively evaluate the safety and effectiveness of prophylactic negative pressure wound therapy (pNPWT) for perineal closed wounds after abdominoperineal resection (APR) in high-risk patients for surgical site infections (SSI).

# Study Subjects and Target Disease

Patients who have undergone APR for malignant rectal tumors.

# Eligibility Criteria

Study subjects will be enrolled only if they meet all the inclusion criteria and do not fall under any of the exclusion criteria.

## Inclusion Criteria

##### Patients undergoing APR* for malignant rectal tumors (*APR is defined as rectal amputation involving a perineal skin incision).

##### Patients who meet the insurance criteria for the PREVENA Incision Management System by satisfying at least one of the following conditions:

###### Undergoing preoperative treatment (chemotherapy or chemoradiotherapy)

###### BMI ≥ 30

###### Diabetic patients with hemoglobin A1c (NGSP) ≥ 7.0%

###### Receiving steroid therapy

###### Undergoing chronic maintenance dialysis

###### In a state of malnutrition, as indicated by one of the following:

1. Unintentional weight loss > 5% within 6 months or > 10% over 6 months
2. BMI < 18.5 for patients under 70 years old, or BMI < 20 for those 70 years and older
3. Calf circumference < 34 cm for men or < 33 cm for women, or skeletal muscle mass < 7.0 kg/m² (men) and < 5.4 kg/m² (women) based on dual-energy X-ray absorptiometry (DXA) or < 7.0 kg/m² (men) and < 5.7 kg/m² (women) based on bioelectrical impedance analysis (BIA)

##### Patients aged 18 years or older with an Eastern Cooperative Oncology Group (ECOG) Performance Status (PS) of 0 or 1

##### Patients who have provided written informed consent for study participation

## Rationale for Inclusion Criteria

Criteria (1) and (2) define the target patient population for this study.

Criterion (3) is set to ensure patient safety.

Criterion (4) is required for ethical study conduct.

## Exclusion Criteria

1. Patients undergoing emergency surgery
2. Patients with a significantly contaminated or infected wound where primary closure is not advisable
3. Patients scheduled to undergo myocutaneous flap reconstruction
4. Patients with known allergies or hypersensitivity to silver or acrylic-based adhesives
5. Any other patients deemed unsuitable for safe study participation by the principal investigator or sub-investigators

## Rationale for Exclusion Criteria

Criteria (1) – (3) are set to minimize factors that could affect the study’s efficacy evaluation.

Criteria (4) – (5) are established for safety considerations.

# Ethical Considerations

## Informed Consent Process

The principal investigator or sub-investigators will provide a thorough explanation of the study to potential participants before obtaining consent. The informed consent documents must be reviewed and approved by the Certified Clinical Research Review Board (CRB) and the hospital director before use. Participants will be given sufficient time to review the study details and ask questions. Written informed consent will be obtained from all participants before study enrollment.

The investigator will ensure that the informed consent form includes the following:

・The name of the physician providing the explanation and the date of explanation.

・The participant’s name and the date of consent.

・A copy of the signed consent form will be provided to the participant.

・The original consent form will be securely stored at the medical institution conducting the study.

If new information arises that may impact the participant’s decision to continue in the study, the investigator will promptly inform the participant. If the consent form is revised, participants will be re-consented using the updated form.

## Preparation and Revision of the Informed Consent Form

The principal investigator is responsible for preparing and revising the informed consent form as needed. Any revisions must be approved by the CRB and the hospital director before use. The consent form must comply with applicable regulations and must not include misleading information.

If new safety or investigational device-related information becomes available that could impact the participant’s willingness to continue, the consent form will be updated and reapproved by the relevant authorities.

## Protection of Personal Information

All study personnel must adhere to applicable laws and regulations regarding personal information protection. Personal information obtained during the study must not be disclosed without justification, even after study completion.

Case report forms will not include personally identifiable information such as names, addresses, or phone numbers. Instead, unique participant identification codes will be used. The correspondence table linking these codes with personal data will be securely stored by the principal investigator.

Study data management personnel will use identification codes or registration numbers to handle data. When publishing study results, every effort will be made to ensure that participants are not personally identifiable.

Data collected before withdrawal of consent may still be used unless the participant explicitly requests complete removal of their data.

## Compensation for Health Damage

If a participant experiences an adverse event related to the study, they will receive appropriate medical care. However, treatment costs will be covered under their health insurance, and no additional financial compensation will be provided. The study does not include clinical research insurance coverage.

## Handling of Incidental Findings

Although this study is not expected to yield significant genetic or health-related findings, any incidental findings relevant to a participant’s health will be communicated to the treating physician or, in the case of healthy volunteers, participants will be advised to seek medical attention.

# Study Design

## Overview of Study Design

This study is a multicenter, single-arm, open-label, non-controlled interventional trial.

## Methods

### Implementation of pNPWT and Treatment Duration

Immediately after perineal wound closure in two or three layers (skin, subcutaneous tissue, and/or levator ani muscle) following APR, the pNPWT device (Prevena Plus Customizable Kit) will be applied to the perineal wound in the operating room. Continuous negative pressure will be applied for 7 days postoperatively. After 7 days, the device will be removed, and routine wound management will be performed. If the pNPWT device detaches within the first 7 days postoperatively, an attempt will be made to reapply it and continue treatment until day 7. If the device is intentionally removed due to adverse events, reapplication will not be performed.

### Standardized Procedures Across Institutions

1. Bowel Preparation

Mechanical and chemical bowel preparation (laxatives and oral antibiotics) will be used. The choice of laxative and administration method is left to the discretion of each institution.

Oral antibiotics (kanamycin 1 g and metronidazole 750 mg) will be administered twice on the day before surgery.

1. Preoperative Hair Removal

No shaving will be performed before surgery; hair removal will be done immediately before the operation.

1. Surgical Site Disinfection

The type of disinfectant used for abdominal preparation is not specified (left to institutional policy). For perineal disinfection, the anus will be temporarily closed before applying disinfectant. The choice of disinfectant for the perineal region is also left to institutional policy.

1. Surgical Approach for APR

Abdominal approach: Either laparoscopic or robotic-assisted surgery

Perineal approach: Both open and endoscopic approaches are acceptable

1. Perineal Wound Closure

The method of perineal wound closure is not specified (left to institutional policy). A typical closure method includes:

Two or three-layer closure involving skin, subcutaneous tissue, and/or levator ani muscle.

Subcutaneous closure: Monofilament absorbable sutures with interrupted or continuous suturing.

Skin closure: Monofilament non-absorbable interrupted sutures (removed after wound healing is deemed complete) or monofilament absorbable subcutaneous sutures.

1. Prophylactic Intravenous Antibiotics

Preoperative: Cefmetazole will be administered within 1 hour before surgery. If the patient has an allergy to cefmetazole, an alternative antibiotic will be selected at the discretion of each institution.

Intraoperative: If using cefmetazole, the same antibiotic will be administered every 3 hours from the initial dose. The dosage and intervals may be adjusted based on renal function and body weight.

Postoperative: No prophylactic intravenous antibiotics will be given after wound closure.

1. Other Measures

Perineal wounds will be irrigated with saline before closure.

A closed suction drain will be placed in the pelvic floor via an abdominal approach.

No perineal drain will be used.

In female patients, a urinary catheter will be maintained for the first postoperative week to prevent perineal wound contamination.

If subcutaneous sutures are used for skin closure, steri-strips will be applied after pNPWT removal to approximate the wound edges.

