### Surgical and Postoperative Information

Clinical tests will be conducted on postoperative day 1 (±1 day allowed), day 3 (±1 day allowed), and day 7 (±2 days allowed).

Surgical information, hospitalization details, surgical outcomes, and pathology results will be recorded as needed.

1. Surgical Information

Date of surgery, duration of surgery, type of disinfectant used, estimated blood loss, presence of blood transfusion, type of antibiotics used.

Abdominal approach: Laparoscopic, robotic-assisted.

Perineal approach: Open, endoscopic.

Skin closure method (interrupted sutures, subcutaneous buried sutures) and type of suture used.

Amount of saline used for wound irrigation.

Lateral lymph node dissection (LLND): Presence or absence (if present, specify left or right).

1. Laboratory Tests

WBC, CRP, other abnormal values (CTCAE Grade ≥2).

1. Hospitalization and Discharge Information

Date of admission, date of discharge or transfer.

1. Surgical Outcomes

Postoperative complications (perineal wound SSI and other complications).

Whether pNPWT was maintained for the full 7-day period.

If pNPWT was removed prematurely, specify on which postoperative day.

1. Pathology Results

ypTNM classification, surgical margin status, assessment of response to chemotherapy.

(Following Japanese Classification of Colorectal, Appendiceal, and Anal Carcinoma, 9th Edition ^(22^).

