### Efficacy Analysis Set (EAS)

The efficacy analysis set (EAS) will include all enrolled patients who had the investigational device applied and did not violate major study protocol criteria (e.g., failure to meet inclusion criteria, lack of consent, unregistered cases, or other significant procedural violations).

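### The efficacy set excludes treated patients for undefined procedural violations, while compliance with most fixed perioperative measures is not a listed data item and exclusions need not be decided blind to SSI

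*Protocol*

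**What the plan says.** **Fixed measures.** Protocol section 6.2.2 sets procedures common to all centres. Examples are "Mechanical and chemical bowel preparation (laxatives and oral antibiotics) will be used", "No shaving will be performed before surgery; hair removal will be done immediately before the operation", "Cefmetazole will be administered within 1 hour before surgery", "No prophylactic intravenous antibiotics will be given after wound closure" and "In female patients, a urinary catheter will be maintained for the first postoperative week to prevent perineal wound contamination". It also requires three-hourly intraoperative redosing, a pelvic suction drain placed from the abdomen, and no perineal drain.

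**Recorded items.** Section 8.2.2 opens its surgical list with "Date of surgery, duration of surgery, type of disinfectant used, estimated blood loss, presence of blood transfusion, type of antibiotics used". It then adds abdominal and perineal approach, skin closure and suture, volume of saline irrigation, and lateral node dissection.

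**Analysis sets.** Section 12.1.1 defines the safety set as every enrolled patient in whom the device was applied, even in part. Section 12.1.2 starts from device-treated patients and removes those who violated major protocol criteria. Its examples end with "lack of consent, unregistered cases, or other significant procedural violations". The word significant is not defined.

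**Decisions and analysis.** Section 13.2 has the principal investigator and the statistical analysis lead discuss problem cases and record the decision with its date. It does not say that they do so before knowing, or without regard to, the SSI result. Section 12.2.1 gives the primary analysis as a proportion with a 95% confidence interval and names no analysis set. The trial is single-arm and open-label (section 6.1).

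**The concern.** The exclusion rule in 12.1.2 can be applied even-handedly only if the same facts are known about every patient and the judgement is made without knowledge of the outcome. The protocol secures neither. For most of the 6.2.2 measures nothing is listed for routine recording, so a deviation may come to light in one patient and not in another. An infected perineal wound is one plausible reason for a closer look at the chart.

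If that happens, infected patients leave the efficacy set more readily than uninfected ones. There is no control arm in which the same selection could offset it, so the loss acts directly on the SSI proportion. Two people then decide what is significant, with no stated protection against knowing the result. These facts also cannot be reliably supplied at analysis if they were not collected uniformly during the trial.

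**Working it through.** The protocol states no figure on this point, so there is none to reproduce. The check has three parts.

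**1. Requirements against recorded items.** Thirteen requirements can be counted in 6.2.2.

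| Requirement in 6.2.2 | Item in 8.2.2 |
| --- | --- |
| Mechanical bowel preparation | none |
| Oral antibiotics | none (unless antibiotic type covers them) |
| Hair removal rule | none |
| Temporary anal closure | none |
| Laparoscopic or robotic approach | yes |
| Intravenous antibiotic within 1 hour | partly: type, not time |
| Redosing every 3 hours | none |
| No intravenous prophylaxis after closure | none (unless antibiotic type covers it) |
| Saline irrigation | yes, as volume |
| Pelvic suction drain | none |
| No perineal drain | none |
| Urinary catheter for one week in women | none |
| Adhesive strips after subcutaneous suture | none |

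Ten of 13 have no item. On the generous reading of antibiotic type it is 8 of 13. Most are unlisted either way.

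**2. Size of a possible bias.** Let x be the number of infections among 50 treated patients and d the share of patients with a deviation, taken as unrelated to SSI. Assume that every deviation is noticed in infected patients and a quarter in uninfected patients, and that each one noticed leads to exclusion. The rate in the efficacy set is then

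x(1 − d) / [x(1 − d) + (50 − x)(1 − 0.25d)].

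The values of d and the detection rates are assumptions. The 12% expected rate, 40% threshold and target of 50 come from section 12.3.

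- x = 6 (12%), d = 0.20: 6 × 0.80 = 4.8; 44 × 0.95 = 41.8; 4.8/46.6 = 10.3%.
- x = 6, d = 0.40: 6 × 0.60 = 3.6; 44 × 0.90 = 39.6; 3.6/43.2 = 8.3%.
- x = 13 (26%), d = 0.20: 13 × 0.80 = 10.4; 37 × 0.95 = 35.15; 10.4/45.55 = 22.8%.
- x = 15 (30%), d = 0.20: 15 × 0.80 = 12; 35 × 0.95 = 33.25; 12/45.25 = 26.5%.

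If deviations are noticed equally often in both groups, the same factor multiplies both counts and cancels, so the expected bias is zero. If they are noticed more often in uninfected patients, the bias is upward. For example, with a true 12%, d = 0.20, and detection of 20% in infected and 80% in uninfected patients: 0.12 × 0.96 = 0.1152; 0.88 × 0.84 = 0.7392; 0.1152/0.8544 = 13.5%.

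**3. Would it change the reading against 40%?** Exact (Clopper-Pearson) 95% upper limits:

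| Infections / patients | Rate | Upper limit |
| --- | --- | --- |
| 6/50 | 12.0% | 24.3% |
| 12/50 | 24.0% | 38.2% |
| 13/50 | 26.0% | 40.3% |
| 12/49 (13/50 less one infected patient) | 24.5% | 38.9% |
| 10/45 (13/50 after the d = 0.20 exclusions, rounded) | 22.2% | 37.1% |
| 14/50 | 28.0% | 42.5% |
| 11/45 (14/50 after the same exclusions, rounded) | 24.4% | 39.5% |
| 12/45 (15/50 after the same exclusions, rounded) | 26.7% | 41.9% |

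Up to 12/50 the limit is below 40% without any exclusion. At d = 0.20 the exclusions move it across at 13 and 14 infections but not at 15. If the true rate is 12%, 13 or more infections in 50 has probability of about 0.5%.

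**The case against.** The strongest reply is that the path from a 6.2.2 deviation to a biased result has several links that the protocol does not state.

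- **Significance.** Section 12.1.2 removes only major or significant violations, and its named examples concern eligibility, consent and registration. Nothing says that a late antibiotic dose or an early catheter removal qualifies. This stands, but nothing rules it out either, and that openness is part of the problem.
- **Analysis set.** Section 12.2.1 does not tie the primary proportion to the efficacy set. This stands too, although the efficacy set is the only one named for efficacy.
- **Detection.** Monitoring checks compliance with the protocol (section 15.1), and medical records are source documents (section 13.3). Both can reveal deviations regardless of infection. A reader might infer that violations will surface mainly after an infection and that the rate is therefore biased downward. The documents do not support that: no section says charts are searched because of infection.
- **Recording.** The schedule table in section 8.3 and the CRF are not shown, and section 13.3 implies that the CRF holds concomitant treatments. Absence from 8.2.2 therefore does not prove that nothing is collected. It shows only that the protocol's own list does not require it.
- **Size.** The deviation and detection rates are assumed, and at the planned 12% no conclusion changes. The primary analysis is also an estimate with an interval, with no stated test against 40%. All of this stands.

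A reader might also object that the objective, to "prospectively evaluate the safety and effectiveness of prophylactic negative pressure wound therapy (pNPWT) for perineal closed wounds", credits pNPWT with a result that the whole package produces. The uncontrolled design is declared, and standardising background care is ordinary practice, so this adds little here.

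**Conclusion.** The point holds in a limited form. Membership of the efficacy set can depend on an undefined term, on facts not listed for every patient, and on decisions not required to be blind to SSI. If 6.2.2 deviations are treated as significant and noticed more often in infected patients, the SSI proportion in that set can be too low. It is not shown that it will be.

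Under the 20% assumption the shift at the planned rate is 1.7 percentage points (12.0% to 10.3%), with no change of conclusion. The reading against 40% is affected only in a narrow band of counts beginning at 13/50, where dropping a single infected patient suffices. The zero-bias case needs both equal detection and deviations unrelated to SSI risk. If patients with deviations have a higher SSI risk, excluding them lowers the rate even with complete recording, so better recording alone is not enough. This is an inexpensive improvement worth making, not a flaw that invalidates the trial.

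**What to change.** 1. In section 12.2.1, estimate the primary SSI proportion in all device-treated patients, using the existing definition in 12.1.1. Keep the efficacy set of 12.1.2 as a sensitivity analysis. This step removes the dependence of the primary result on exclusions for violations.
2. In section 8.2.2, add yes/no, time or day items for the 6.2.2 measures not yet listed, completed for every patient. They include bowel preparation and oral antibiotics, times of first and repeat intravenous doses, pelvic drain, perineal drain, and catheter days in women.
3. In section 12.1.2, say which procedural violations count as significant, and state that they are judged from these items by people blind to SSI status. Refer to this rule in 13.2.

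The cost is a few more CRF fields filled from the operative and ward record and a few sentences of protocol text. No extra visits or patients are needed. The primary rate may come out slightly less favourable than in the efficacy set. No change to the clinical measures themselves is proposed.
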